### 1.2. Aims and Hypotheses

Our aims are the following:

-The primary aim of the current pilot study is to investigate the association between baseline fatty acid profiles and the magnitude of antidepressant treatment response and to generate preliminary effect size estimates to inform the design of a future adequately powered study examining the predictive utility of fatty acid biomarkers in depression.-The secondary objective is to investigate the association between the erythrocyte membrane and serum fatty acid profiles and the clinical presentation of depressive disorders, encompassing the severity of depressive symptoms, anxiety symptoms, and stress-related symptoms, as assessed by the Depression, Anxiety and Stress Scales (DASS-42) and the Beck Depression Inventory-II (BDI-II).

We assume that the profile of long-, medium-, and short-chain fatty acids in blood may be associated with the course and clinical picture of depression. The main confounding factors are hypothesized to be diet, physical activity, and somatic comorbidities, with their treatment.

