The Frequency Questionnaire (FFQ-6) is a dietary assessment tool designed to evaluate habitual food consumption patterns over a specified retrospective period. The questionnaire focuses on the frequency of intake of selected food groups. Participants are asked to report how often they consume specific food items or food categories using predefined frequency options. The FFQ-6 enables estimation of dietary patterns, nutrient intake proxies, and adherence to specific dietary behaviors, including those relevant to lipid and fatty acid intake. The study will use the Polish validated version of the FFQ-6 questionnaire by Niedzwiedzka et al. [33].

Dietary data obtained from the FFQ-6 will be aggregated into predefined food groups for the purpose of statistical adjustment. The following groups will be distinguished: sweets and snacks, dairy and eggs, cereal products, oils, fruits, vegetables and seeds, meat (including fish and its subcategories of processed and unprocessed meat), alcohol, and drinks excluding water. Selected groups will be further subdivided into processed and unprocessed subcategories. For each group, a dietary index will be calculated based on the mean consumption frequency of constituent products. A composite processed food index will additionally be derived from items classified as processed across multiple food categories. These indices will serve as dietary covariates in regression analyses examining fatty acid profiles in relation to clinical outcomes [34].

The International Physical Activity Questionnaire (IPAQ) was developed by an international consortium to provide a standardized measure of physical activity suitable for international and cross-cultural use. A large reliability and validity study conducted across 12 countries (including translation and cultural adaptation procedures) showed acceptable measurement properties [35]. The study will use the Polish version of the IPAQ compiled by Biernat et al., which has been officially translated and registered for use in Poland and enables classification of physical activity into internationally standardized MET-minute categories [36].

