Antidepressant class will initially be categorized as selective serotonin reuptake inhibitor, serotonin–norepinephrine reuptake inhibitor, or other. Categories may be combined if their sizes do not permit reliable estimation. The robustness of the primary findings will be examined in sensitivity models additionally accounting for relevant dietary, metabolic, lifestyle, and treatment-related factors. These may include fish and seafood intake, a plant- and fiber-rich food index, body mass index or waist circumference, physical activity, smoking, alcohol consumption, comorbidities, concomitant medications, psychotherapy, adherence, hospitalization status, and treatment modifications. Because of the limited sample size, these variables will not all be included simultaneously in a single model. Secondary binary outcomes at week 6 will include treatment response, remission, and minimal clinically important improvement. Their associations with individual fatty acids will be examined using separate exploratory logistic regression models with a limited number of prespecified covariates. Penalized likelihood estimation may be used in the event of complete or quasi-complete separation. 

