Longitudinal changes in DASS-42 subscales and WHOQOL-BREF domain scores will be examined using analogous mixed-effects models. Baseline relationships between fatty acid measures and psychometric variables will be assessed using Pearson or Spearman correlation coefficients, as appropriate. Principal component analysis will be applied to standardized erythrocyte fatty acid variables to identify broader fatty acid patterns and reduce dimensionality. The number of retained components will be determined using parallel analysis and inspection of the scree plot. Component scores will be evaluated in exploratory models analogous to those used for individual fatty acids. PCA will not be applied to the three serum SCFAs. The Benjamini–Hochberg false discovery rate procedure will be used to account for multiple testing involving individual fatty acids. Correction will be applied separately to the primary family of analyses involving the week 6 BDI-II outcome and to each secondary outcome family. Both unadjusted *p*-values and false-discovery-rate-adjusted *q*-values will be reported. Missing follow-up data will be minimized through regular contact with participants and electronic questionnaires requiring completion of all items. The timing and reasons for missed assessments and withdrawal will be recorded. Mixed-effects models will use all available repeated observations and will provide valid estimates under the missing-at-random assumption. Missingness patterns will be examined descriptively, and the potential impact of departures from this assumption will be evaluated in sensitivity analyses if the amount of missing data permits. Missing baseline fatty acid measurements will not be imputed. The study is not designed to establish clinical cut-offs or validate a clinical prediction tool. If an exploratory combined prediction model is developed, its apparent performance and optimism will be assessed using bootstrap resampling. Such findings will require external validation in future adequately powered studies.

Analyses will be performed using Statistica 13.3 and the R software 4.6.1.

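### The baseline fatty acid–symptom associations have only unadjusted correlations assigned to them, although the protocol names their main confounders, and two dietary covariates in section 2.6 do not match the indices defined in section 2.3

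*Protocol article*

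**What the plan says.** Section 1.2 of the protocol article sets the aim: "The secondary objective is to investigate the association between the erythrocyte membrane and serum fatty acid profiles and the clinical presentation of depressive disorders", with severity measured by BDI-II and DASS-42. The same section then states: "The main confounding factors are hypothesized to be diet, physical activity, and somatic comorbidities, with their treatment".

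Section 2.6 gives the method for the baseline part of that aim: "Baseline relationships between fatty acid measures and psychometric variables will be assessed using Pearson or Spearman correlation coefficients, as appropriate". It mentions neither covariates nor partial correlation.

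Wider adjustment appears earlier in section 2.6, with a limited scope: "The robustness of the primary findings will be examined in sensitivity models additionally accounting for relevant dietary, metabolic, lifestyle, and treatment-related factors". The candidates are optional: "These may include fish and seafood intake, a plant- and fiber-rich food index, body mass index or waist circumference, physical activity, smoking, alcohol consumption", followed by comorbidities, concomitant medications and treatment-related items.

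Section 2.3 defines FFQ-6 food groups for use in adjustment. Each is scored as the mean consumption frequency of its products. Fish falls in the group described as "meat (including fish and its subcategories of processed and unprocessed meat". On the use of the indices, section 2.3 says: "These indices will serve as dietary covariates in regression analyses examining fatty acid profiles in relation to clinical outcomes".

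**The concern.** The plan identifies a source of bias and then assigns the affected analysis a method that cannot address it. Section 2.4 calls BMI and waist circumference essential covariates when circulating fatty acids are studied, and says erythrocyte composition reflects diet over the preceding 90–120 days. By the protocol's own account, then, diet and adiposity act on the exposure. If they also relate to symptom severity, a raw correlation mixes their effect with any association specific to the fatty acid. It may be too large, too small or of the wrong sign.

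This matters in an exploratory study too. A pilot meant to supply effect sizes for a later study passes on whatever bias those estimates contain.

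The dietary covariates add a smaller problem. Fish/seafood intake and a plant/fiber index are the diet variables most directly tied to EPA/DHA and to the short-chain acids. Section 2.6 relies on them, but section 2.3 does not define them.

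**Working it through.** The plan gives no figure to reproduce. The check has a textual part and an illustrative part.

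**Which analysis adjusts for what (protocol article)**

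| Analysis | Covariates | Uses the section 1.2 confounders? |
|---|---|---|
| Baseline correlations (2.6) | none | no |
| BDI-II mixed models (2.6) | age, sex, antidepressant class | no |
| DASS-42 mixed models, described as analogous (2.6) | same, by analogy | no |
| Sensitivity models (2.6) | optional diet, activity, comorbidity and others | yes, for the primary findings only |
| Regressions with dietary indices (2.3) | food-group indices | diet only; section 2.6 has no such regression for the baseline associations |

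**Dietary covariates.** The groups in section 2.3 are sweets and snacks; dairy and eggs; cereal products; oils; fruits, vegetables and seeds; meat including fish; alcohol; and drinks other than water. A composite processed-food index is added. Section 2.6 wants "fish and seafood intake, a plant- and fiber-rich food index, body mass index or waist circumference". Neither of the two diet variables is on the section 2.3 list. A plant/fiber index might be built from fruit, vegetable, seed and cereal items, but no rule is given.

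**Illustrative size of the bias.** Input from the documents: n = 60. Assumed, because the documents give no confounder strengths: one confounder C correlated with the fatty acid (x) and the symptom score (y).

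r_xy = r_partial × √[(1 − r_xc²)(1 − r_yc²)] + r_xc × r_yc

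With r_partial = 0 this reduces to r_xy = r_xc × r_yc. The chance of two-sided p < 0.05 comes from Fisher's z: Z = atanh(r_xy) × √57, and P = Φ(Z − 1.96) + Φ(−Z − 1.96).

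| r_xc = r_yc | Spurious r | Z | P(p < 0.05) |
|---|---|---|---|
| 0.2 | 0.04 | 0.30 | about 6% |
| 0.3 | 0.09 | 0.68 | about 10% |
| 0.4 | 0.16 | 1.22 | about 23% |
| 0.5 | 0.25 | 1.93 | about 49% |

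Masking is equally possible. With r_xc = 0.5, r_yc = −0.5 and a true partial correlation of 0.30, r_xy = 0.30 × √(0.75 × 0.75) − 0.25 = 0.225 − 0.25 = −0.025.

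**Effect of the multiplicity correction.** Section 2.4 lists 29 fatty acids (internal standard excluded) plus three short-chain acids, so 32 analytes. The strictest Benjamini–Hochberg step for one set of 32 is 0.05/32 = 0.0016, with a normal critical value of 3.16. If only one analyte were confounded and had to pass that step, the 0.5 row would give about Φ(1.93 − 3.16) = 11%. If many analytes shared the confounder, the threshold would loosen and the figure would rise. The estimate stays at 0.25 in either case, because the correction acts on p-values and not on bias.

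**Cost of adjusting.** Critical |r| = t/√(df + t²), with df = n − 2 − k for k covariates.

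| k | df | t | Critical \|r\| at n = 60 |
|---|---|---|---|
| 0 | 58 | 2.002 | 0.254 |
| 3 | 55 | 2.004 | 0.261 |
| 5 | 53 | 2.006 | 0.266 |
| 7 | 51 | 2.008 | 0.271 |

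**The case against.** Four points can be made for the plan.

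1. *A reader might infer that the secondary objective has no covariate-adjusted analysis at all.* That goes too far. The objective is not explicitly limited to baseline, and the BDI-II and DASS-42 mixed models contain a fatty acid main effect. With categorical time and baseline as reference, that term is a baseline association adjusted for age, sex and antidepressant class. However, the protocol does not designate it for this objective, and it includes none of the section 1.2 confounders.

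2. *A reader might infer that fish is lost within meat throughout, so that EPA and DHA would be adjusted with a meat index.* The documents do not support this. Section 2.6 names fish and seafood separately, and the FFQ-6 is collected by food item or category, so the variable can probably be derived. What stands is a mismatch of definitions between the two sections.

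3. *All analyses are declared exploratory, and raw correlations are a normal descriptive step.* This is correct, and no confirmatory error rate is at risk. Nor is 49% the error rate of the planned procedure: it is the top of an assumed range, before the false discovery rate correction. Biased effect estimates are still a poor product for a pilot whose purpose includes estimating effects.

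4. *Covariate lists are usually left to a fuller document.* That would excuse silence. Here the article states a method, and it does not fit the article's own account of confounding or its stated use of the dietary indices.

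There is also a fair argument against adjustment itself. Diet is a main source of variation in EPA and DHA, and depression may change diet, so conditioning on diet can remove part of the signal of interest. This is a reason to report both estimates. It is not a reason to report only the raw one.

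**Conclusion.** The point holds as a gap between the plan's stated confounders and the analysis assigned to the baseline associations, together with an inconsistency between sections 2.3 and 2.6 over fish/seafood and the plant/fiber index. It affects interpretation of the secondary objective and the effect sizes carried forward. It does not touch the primary contrast, whose sensitivity models may include these factors.

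The size of the bias cannot be derived from the documents. The range of 0.04 to 0.25 for the spurious correlation, and of about 6% to 49% for uncorrected rejection, rests on assumptions: a single confounder, equal correlations of 0.2 to 0.5 with both variables, no other association, complete data on 60 participants and the Fisher approximation. Weak confounding would do little harm; opposite-signed confounding could hide a real association. The change is worth making because it uses data already planned and costs little precision.

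**What to change.** **Section 2.6.** Keep the Pearson or Spearman coefficients and label them descriptive. Beside them, for each baseline score and each standardized fatty acid, report a linear regression or partial correlation adjusted for age, sex, BMI or waist circumference, and a small prespecified set taken from section 1.2: a diet index, physical activity, and comorbidity with its treatment. Fix the set before outcome data are examined. Leave hospitalization status out of the main adjusted model, because it may be a consequence of severity; it can be shown as a separate sensitivity result. Report both estimates with confidence intervals.

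**Section 2.3.** Define fish/seafood as an index separate from meat, state which items form the plant/fiber index, and use the same names in section 2.6.

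**Cost.** Changes of wording and recoding of FFQ-6 items already planned for collection. The critical |r| rises from 0.254 to about 0.266 with five covariates, or 0.271 with seven if comorbidity and treatment take two terms. Where a covariate is closely related to the fatty acid, the adjusted slope also becomes less precise: if covariates explain 25% of the fatty acid's variance (assumed), its standard error grows by 1/√0.75 = 1.15 for the same residual variance. Part of the diet-driven signal may be removed as well, which the side-by-side presentation makes visible.

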## 3. Discussion

As highlighted earlier, the rising prevalence of depressive disorders has intensified the need for effective predictors of antidepressant treatment response. This growing clinical challenge is reflected in the increasing scientific interest in identifying reliable biomarkers of treatment efficacy, which has led to a substantial expansion of research in this area. The studies summarized in Table 2 illustrate the diversity of approaches and findings to date, underscoring both the potential and the current limitations of existing predictors of antidepressant treatment outcomes.

Compared with previous studies focusing primarily on selected inflammatory markers or individual lipid fractions, the present prospective pilot study is distinguished by its comprehensive assessment of circulating fatty acids, including short-, medium-, and long-chain fatty acids. Importantly, the inclusion of short-chain fatty acids, which are closely linked to gut microbiota metabolism, represents a novel approach in the context of antidepressant treatment response. The prospective design and 12-week follow-up allow for evaluation of fatty acids as potential predictors rather than correlates of clinical response, while the naturalistic treatment setting enhances the clinical relevance of the findings.

While the current pilot study is not powered to define definitive clinical diagnostic thresholds, it serves as a critical translational stepping stone. The primary objective is to estimate the effect sizes and variance of fatty acid parameters in relation to antidepressant response, and these estimates will allow for precise a priori sample size calculations for subsequent large-scale, multi-center cohorts designed specifically to establish predictive performance metrics, including diagnostic thresholds derived from ROC-based analyses with associated sensitivity, specificity, and positive predictive values.

Regarding personalized antidepressant strategies, we hypothesize that fatty acid profiling could eventually facilitate a ‘match/mismatch’ clinical approach. Identifying a patient with a low baseline EPA:DHA ratio, reduced erythrocyte EPA and DHA levels, an elevated AA/(EPA + DHA) ratio, or depleted SCFA concentrations—potentially in combination with elevated inflammatory markers such as CRP or NLR, and indicators of gut microbiota dysregulation—may indicate an underlying inflammatory or gut-dysbiosis-associated phenotype of depression. In clinical practice, such a biomarker profile could flag a patient likely to respond poorly to a standard monotherapy but who might benefit from targeted adjunctive interventions—such as nutritional or anti-inflammatory strategies—tailored to their metabolic phenotype. Furthermore, by adjusting for dietary intake assessed with the FFQ-6 and anthropometric parameters, this study will provide foundational data on whether fatty acid thresholds need to be personalized based on metabolic characteristics, bringing precision psychiatry closer to routine clinical implementation.

Several limitations of the present study should be acknowledged. First, depressive symptom severity and treatment response will be assessed exclusively using self-reported measures, namely the BDI-II and DASS-42, without the inclusion of clinician-rated scales such as the Hamilton Depression Rating Scale (HAM-D) or the Montgomery–Åsberg Depression Rating Scale (MADRS). This should be considered when interpreting treatment response and remission outcomes.

Second, the study does not include a healthy control group. While the primary objective is to identify predictors of antidepressant treatment response rather than to characterize fatty acid abnormalities relative to a reference population, the absence of controls limits the ability to contextualize baseline fatty acid profiles and to draw conclusions regarding disease-specific alterations in lipid metabolism.

Third, participants will be recruited exclusively from clinical settings. While this approach ensures diagnostic rigor and clinical homogeneity of the study sample, it may limit the generalizability of findings to individuals with depressive disorders who do not seek specialist care or who are managed outside of institutional healthcare settings.

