### 2.2. Sample Size

As this is a prospective pilot study, the planned sample size was not based on a formal confirmatory power calculation. Currently, there is limited data allowing for a reliable estimation of the expected effect size for the association between baseline fatty acid profiles and antidepressant treatment outcomes. Therefore, the planned recruitment of 60 participants was determined pragmatically, based on the feasibility of recruitment, follow-up, and biological sample processing and on the aim of obtaining preliminary estimates of variability, effect sizes, responder proportions, and attrition rates for a future adequately powered study. Based on previous studies, the anticipated treatment response rate is approximately 50% [24]. Therefore, before accounting for attrition, the planned sample of 60 participants may yield approximately 30 responders and 30 non-responders. This estimate is provided to describe the expected sample distribution and does not imply that the study is adequately powered to develop or validate a multivariable prediction model [25].

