### 2.6. Statistical Analysis

All analyses will be exploratory and hypothesis-generating. Continuous variables will be summarized using means and standard deviations or medians and interquartile ranges, as appropriate, and categorical variables as counts and percentages. Markedly skewed fatty acid variables may be transformed. Fatty acid measures will be standardized to facilitate comparison of effect estimates. Results will be reported with 95% confidence intervals, and *p*-values will be interpreted in the context of the pilot nature of the study. The primary endpoint will be the change in BDI-II total score from baseline to week 6. Associations between individual baseline fatty acids and depressive symptom trajectories will be examined using separate linear mixed-effects models estimated with restricted maximum likelihood. Repeated BDI-II scores obtained at baseline and at weeks 3, 6, and 12 will constitute the dependent variable. Models will include time, the standardized fatty acid measure, the fatty acid-by-time interaction, age, sex, and antidepressant class as fixed effects, with a participant-specific random intercept. The prespecified primary contrast will represent the association between the baseline fatty acid measure and change in BDI-II score from baseline to week 6. Fatty acids will be analyzed individually rather than entered simultaneously into a single conventional multivariable model.

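### The Discussion promises precise sample-size calculations for later cohorts, which effect sizes from 60 participants and 32 separately modelled fatty acids cannot support

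*Protocol article*

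**What the plan says.** The Discussion names estimation of effect sizes and of variance as the primary objective and states that "these estimates will allow for precise a priori sample size calculations for subsequent large-scale, multi-center cohorts". Those cohorts are meant to establish predictive performance, including diagnostic thresholds.

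Other sections are more cautious. Section 1.2 includes in the primary aim "to generate preliminary effect size estimates to inform the design of a future adequately powered study". Section 2.2 says that "the planned recruitment of 60 participants was determined pragmatically", that "the planned sample size was not based on a formal confirmatory power calculation", and that "there is limited data allowing for a reliable estimation of the expected effect size". It too describes the expected outputs as preliminary.

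On the analysis, section 1.1 declines to prespecify a single fatty acid hypothesis. Section 2.6 fits a separate mixed model for each acid, declares all analyses exploratory, and adds that "Results will be reported with 95% confidence intervals". Benjamini–Hochberg correction is applied across the individual acids. Optimism is addressed in one place only: "If an exploratory combined prediction model is developed, its apparent performance and optimism will be assessed using bootstrap resampling".

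**The concern.** Supplying effect sizes for the next study is part of the pilot's primary aim, so a statement about how good those effect sizes will be concerns its main product. Precision for effect sizes does not follow from 60 participants, and the word contradicts the two sections that set the aim and the sample size.

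There are two separate problems. The first is sampling error: even one acid chosen in advance would leave a wide range of plausible sample sizes. The second is selection: when many acids are estimated and none is named as the lead, the acid that stands out does so partly by chance, and its raw estimate is too large on average. A later study sized on that raw figure could be too small, or could pursue an acid with no real association.

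**Working it through.** **The plan's own figure.** The only sample-size arithmetic given is the expected split. Section 2.2 says "the anticipated treatment response rate is approximately 50" per cent, and 60 × 0.50 = 30 responders and 30 non-responders, before attrition. This reproduces. The figure of 60 is pragmatic and has no formula behind it.

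**Inputs from the article.**
- n = 60 (section 2.2).
- Panel: 29 named acids from C10 to C24 in section 2.4, not counting the internal standard C21:0, plus acetate, propionate and butyrate. 29 + 3 = 32.
- 95% confidence intervals (section 2.6).

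**Assumptions.**
- The future study has 80% power at two-sided 5%; the article gives neither.
- No effect size is given, so a range of observed r is shown.
- No attrition rate is given, so 10% and 20% are shown as illustrations.
- A simple correlation r stands in for the acid-by-time contrast of the adjusted mixed model. It indicates the order of magnitude and does not reproduce that model.

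**Step 1: sampling error of one effect.** The interval on the Fisher scale is atanh(r) ± 1.96/√(n − 3). For r = 0.30 and n = 60, atanh(0.30) = 0.3095 and 1/√57 = 0.1325, so the limits are 0.3095 ± 0.2596. Transformed back, the 95% CI is 0.050 to 0.515.

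The required sample size is N = ((1.960 + 0.842)/atanh(r))² + 3, rounded up. At the lower limit N = 3,154, at the point estimate 85, and at the upper limit 28. The ratio is 3,154/28, about 113.

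The result depends strongly on the observed r (n = 60, complete data):

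| Observed r | 95% CI | N at lower limit | N at upper limit | Ratio |
|---|---|---|---|---|
| 0.25 | −0.004 to 0.474 | unbounded | 33 | – |
| 0.30 | 0.050 to 0.515 | 3,154 | 28 | 113 |
| 0.35 | 0.105 to 0.555 | 704 | 24 | 29 |
| 0.40 | 0.163 to 0.594 | 295 | 20 | 15 |
| 0.50 | 0.282 to 0.669 | 97 | 15 | 6.5 |

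Attrition widens the range. At r = 0.30 the ratio is about 237 with 54 completers (10% loss) and about 1,044 with 48 (20% loss).

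**Step 2: the variance.** The Discussion also names variance. The 95% CI for a standard deviation at n = 60 runs from √(59/χ²(0.975; 59)) = 0.85 to √(59/χ²(0.025; 59)) = 1.22 times the estimate, about a two-fold range in variance. That is useful for planning.

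**Step 3: selection among 32 estimates.** Simulated mean of the largest |r| at n = 60 when no acid has any effect:

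| Correlation among the 32 acids | Mean largest absolute r |
|---|---|
| Independent | 0.30 |
| Blocks correlated at 0.6 | 0.29 |
| All pairs 0.3 | 0.29 |
| All pairs 0.5 | 0.27 |
| All pairs 0.7 | 0.24 |

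In the independent case the 5th to 95th percentiles are 0.22 to 0.40. A study sized on a chance r of 0.30 would plan for N = 85.

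**Step 4: the planned safeguards.**
- Benjamini–Hochberg acts on p-values and leaves estimates unchanged. An acid passing at 5% as the only hit needs p ≤ 0.05/32 = 0.0016, which is |r| of about 0.40 at n = 60, so an estimate that survives the filter has been selected for being large.
- The 95% CIs show sampling error but do not allow for selection.
- The bootstrap optimism step is tied to a combined model that may never be built.

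**The case against.** The strongest reply is that this is one adjective in the Discussion. Sections 1.2, 2.2 and 2.6 are properly hedged, and no estimand, test or sample size in this pilot depends on it. That stands, and it limits the point to the claim and the reporting. It does not remove the point, because the sentence describes what the Discussion itself calls the primary objective.

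A reader might infer that the plan will size the next study on the largest observed effect. The article does not say so and gives no rule for choosing a planning value. What it does show is a panel with no lead candidate, which makes selection the likely route and leaves it unguarded.

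A reader might also infer that the pilot would launch a study on noise. The documents do not support that either. At n = 60 an observed r of 0.30 has p of about 0.02, and its q-value can be as high as 32 × 0.02 = 0.64. In simulations with 32 independent null acids the median smallest q is about 0.50, and q falls below 0.05 in about 5% of runs. Chance winners would usually be reported as non-significant. The safeguard limits false positives, but it does not correct effect size.

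Other qualifications also stand. The hundred-fold range holds only near an observed r of 0.30. The null maximum of 0.30 needs independent acids. The later cohorts are meant to estimate predictive performance, so sizing a test of r = 0 is only an illustration. Requiring one particular lower-confidence-limit rule of a study not yet written would be a matter of preference.

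**Conclusion.** The point holds as a mismatch between a stated property and the design. Sixty participants cannot give precise effect sizes for planning, and the article contradicts itself by calling the same estimates preliminary elsewhere. Under the assumptions stated, required N spans about 113-fold at an observed r of 0.30, has no upper bound at 0.25 or below, and still spans 6.5-fold at 0.50. The raw maximum over 32 acids is inflated, averaging 0.24 to 0.30 with no true effect, depending on how correlated the acids are.

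The variance estimate is adequate, the pilot's conduct and analyses remain valid, and it can still serve its purpose. The change is worth making because it costs little and concerns the main output.

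**What to change.** In the Discussion, replace *precise* with *preliminary, with wide uncertainty*, in line with sections 1.2 and 2.2.

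In section 2.6, add that the individual-acid effects on week 6 BDI-II change will be reported both as raw estimates with 95% CIs and as selection-corrected values. Suitable methods are empirical-Bayes shrinkage across the 32 effects, or a bootstrap that repeats the selection step; either would do. Add that planning of a future study will use the corrected values or a minimum relevant effect, rather than the largest raw estimate.

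The cost is one reworded sentence, a short addition to the analysis section and a little more computing. The planning effects will look less favourable. Recruitment, assays and visits do not change.
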